#### 2. Activation patterns across stimulus durations

This analysis will target the relation between the temporal duration of the experience and the neural responses. Since subjects will observe clearly visible isolated stimuli at fixation and without competition, we assume that they will experience the stimuli for as long as they are on-screen, in particular because subjects’ fixation (via eye-tracking) will be constantly monitored (see the OSF page for a control experiment evaluating visibility of long-duration task irrelevant stimuli).

Here, we will evaluate the neural responses associated with the maintenance of a percept in consciousness. Specifically, we will investigate the temporal profile of activation evoked by stimuli of different durations as well as the temporal profile of informational content of the neural responses throughout the duration of the stimulus. For the former, we will compare activation levels between conditions (defined by stimulus duration) in four different time windows: (1) 300–500 ms, (2) 800–100 ms, (3) 1300–1500 ms, and (4) 1800–2000 ms using linear mixed models. For the latter, we will combine temporal generalization [53] and representational similarity analysis [RSA; 48] approaches: in long duration trials, stimulus category (as well as orientation) will be decoded in a temporal generalization fashion (testing for generalization of neural patterns containing the content specific information across time). Representational similarity analysis will then be employed to compare the resulting temporal generalization matrix to the predictions of the theories in the specified time windows.

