GNW predicts ignitions within PFC following stimulus onset and possibly also during stimulus offset, constituting updates to conscious perception, with virtually no activity between updates [except for occasional stochastic bursts of spontaneous reactivation; 54]. Thus, for consciously perceived but task-irrelevant stimuli, neural activation is predicted to reflect an interaction between duration and time window in the PFC, such that activation is maximal in windows following stimulus onset and offset and minimal elsewhere. GNW further predicts that the patterns of activation will be consistent and content-specific between the windows where activation is expected to be maximum, whereas in the windows of minimal activation, there should be no content-specific activation. This translates in expected temporal generalization of decoding accuracy between the onset and offset burst with no generalization in between. This prediction can be translated in a model matrix to be correlated with the obtained temporal generalization results. IIT predicts sustained, content-specific activity patterns in posterior cortex throughout the duration of the percept (after the initial transient response). Therefore, activation levels within posterior areas should be higher for longer-duration (and consciously seen) than shorter-duration (and no longer seen) stimuli during analysis time windows 2 and 3. In addition, temporal generalization of decoding accuracy should be evident for as long as the stimuli are consciously experienced, and will be tested via correlation with a different model matrix than for GNW.

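### A correlation with each theory's own model matrix does not show that the predicted temporal generalization occurred, so data lacking it can be credited as support

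*Protocol article*

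**What the plan says.** The relevant text is in the Protocol article, Experiment 1, Planned analyses and expected outcomes, section 2 (Activation patterns across stimulus durations).

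- **Data.** The analysis uses 1500 ms stimuli: "in long duration trials, stimulus category (as well as orientation) will be decoded in a temporal generalization fashion". Representational similarity analysis is then used to "compare the resulting temporal generalization matrix to the predictions of the theories in the specified time windows".
- **IIT prediction (posterior cortex).** "temporal generalization of decoding accuracy should be evident for as long as the stimuli are consciously experienced". The test is that this "will be tested via correlation with a different model matrix than for GNW".
- **GNW prediction (PFC).** "This translates in expected temporal generalization of decoding accuracy between the onset and offset burst with no generalization in between". On the test: "This prediction can be translated in a model matrix to be correlated with the obtained temporal generalization results". The offset part is hedged: "GNW predicts ignitions within PFC following stimulus onset and possibly also during stimulus offset".
- **Windows.** They are listed with the activation analysis: "1) 300–500 ms, (2) 800–100 ms, (3) 1300–1500 ms, and (4) 1800–2000 ms using linear mixed models". The second is taken here to end at 1000 ms.

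The section sets no requirement on particular off-diagonal cells, names no competing non-generalizing model, and does not say what size or significance of correlation counts as support. The Analysis approach section leaves analysis details to phase 2 and the amended preregistration.

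**The concern.** The predictions concern particular cells of the matrix: whether a decoder trained at one time works at a distant time. The named statistic summarizes similarity over the whole matrix. A sustained IIT block contains its own diagonal, so ordinary moment-by-moment decoding already resembles it. A GNW matrix contains the onset-by-onset and offset-by-offset blocks, so two bursts resemble it even if their patterns are unrelated, although the section expects the patterns to be consistent between those windows.

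At stake is one of the three predictions that the overview of operational hypotheses singles out for Experiment 1. The Aim of Experiment 1 calls sustained activity critical for IIT. The study is meant to arbitrate between the theories, so a test that can pass a theory on data lacking its predicted feature weakens that purpose. Repeating the same statistic on the second half of the data would repeat the error, not expose it.

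**Working it through.** The protocol gives no figure for this test, so there is none to reproduce. The check asks what the named statistic returns for patterns that lack the predicted feature.

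**Assumed matrices.** Four windows (300–500, 800–1000, 1300–1500, 1800–2000 ms) give a 4 × 4 matrix with N = 16 cells. The IIT model is 1 in the block of windows 1–3 (9 cells), or of windows 2–3 (4 cells) if the initial transient is left out. The GNW model is 1 in windows 1 and 4 and their cross cells (4 cells). For a 0/1 pattern with *a* ones, a model with *b* ones and *c* shared ones:

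r = (N·c − a·b) / √[a(N − a)·b(N − b)]

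| Noise-free pattern | Model | a, b, c | r |
|---|---|---|---|
| Diagonal only, windows 1–3 | IIT, windows 1–3 | 3, 9, 3 | 21/√(39·63) = 0.42 |
| Diagonal only, windows 1–3 | IIT, windows 2–3 | 3, 4, 2 | 20/√(39·48) = 0.46 |
| Diagonal only, windows 1–3 | GNW | 3, 4, 1 | 4/√(39·48) = 0.09 |
| Two bursts, no cross-generalization | GNW | 2, 4, 2 | 24/√(28·48) = 0.65 |
| Onset only | GNW | 1, 4, 1 | 12/√(15·48) = 0.45 |
| Onset only | IIT, windows 1–3 | 1, 9, 1 | 7/√(15·63) = 0.23 |
| Onset only | IIT, windows 2–3 | 1, 4, 0 | −4/√(15·48) = −0.15 |

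**Finer grid.** With 20 ms steps over 0–2000 ms, and the analysed region taken as the full matrix, 300–2000 ms or the four windows, a diagonal code of width (SD) 25 to 200 ms correlates 0.19 to 0.62 with the IIT matrix and 0.04 to 0.12 with the GNW matrix. Two unrelated bursts correlate 0.66 to 0.70 with the GNW matrix.

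**Illustrative rejection rates.** The assumed rule is a one-sided 5% t-test of subject correlations against zero. Sample sizes come from Participants, sample size, exclusion criteria and stopping rule: 100 M-EEG subjects less 20% attrition is 80, and half of that is 40.

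- 4 × 4 grid, unit noise per cell, signal 0.5 or 1 noise SD, n = 40: the diagonal-only code is significant for IIT in about 64% or 99% of simulated studies, and the two unrelated bursts for GNW in 82% or 100%. At n = 80 the diagonal-only figures are 88% and 100%. With no signal, rejection is about 5%.
- Finer grid, noise SD 0.03 in 100 ms blocks, decoding excess 0.02, n = 40: the diagonal code (width 50 ms) is significant for IIT in 91–97%, and the two unrelated bursts for GNW in 100%.

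**Do the off-diagonal cells separate the cases?** Windows 1 and 3 are at least 1300 − 500 = 800 ms apart. A Gaussian diagonal code of width 200 ms therefore gives at most exp(−800²/(2·200²)) = exp(−8) ≈ 0.0003 of its peak there, while a stable code gives its full value. In the onset-by-offset cells, two unrelated bursts and an onset-only response both give zero. On the 4 × 4 grid at n = 40, testing these cells held false support to about 4–7%, with about 100% power for the true patterns.

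**Does a joint regression suffice?** With the two theory matrices plus diagonal and onset-block matrices, two unrelated bursts still gave a significant GNW coefficient in 26% or 55% of studies at n = 40. A code lasting only through windows 1–2 gave a significant IIT coefficient in 52% or 96%.

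**The case against.** The strongest reply is that the decision rule tested above is not the protocol's. Nothing printed says that a correlation above zero counts as support. The matrices are not given, the outcome scheme in Fig 1 is not shown, and details are openly deferred to the preregistration. This stands as far as it goes: a reader might infer that a non-generalizing result *will* be scored for a theory, and the document does not say so. But the article does name the statistic, and that statistic does not target the stated prediction. Deferring details does not change that.

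A second reply is that maintenance is not tested by correlation alone. Mixed models compare activation by duration and window, and comparing the matrix with both theories' predictions could include a contest between models. The mixed models are a separate test of maintenance, but of activation level, not of content generalizing over time. A contest between the two matrices would not help either: a diagonal code correlates more with the IIT matrix than with the GNW matrix.

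A third tempting inference is that one onset response would count for both theories. The text does not support it. GNW commits to offset ignition only as a possibility, so an onset-only result in PFC is not plainly contrary to it. For IIT, the sustained pattern is described as following the initial transient, and a matrix that starts after it gives r = −0.15. The theories are also tested in different regions. Onset-only is therefore the weaker example.

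**Conclusion.** The concern holds in this form: the only test named for each theory's temporal-generalization prediction is correlation with its own model matrix, and a positive correlation does not establish the predicted generalization. The clear cases are a purely diagonal code for IIT (r about 0.2 to 0.6, depending on the assumed matrix and code width) and unrelated onset and offset bursts for GNW (r about 0.65 to 0.70). Data of either kind can be credited as support.

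The direction for these two cases held under every matrix coding and analysed region tried. The rejection percentages are illustrative: they rest on assumed matrices, noise, signal size and a rule of r above zero.

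**What to change.** Before the phase 2 lock, keep the model correlations as a description and add a criterion on the cells that carry each prediction:

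- **IIT, posterior cortex:** group-level decoding above chance in the cross-window cells across the stimulus duration, including the earliest by latest sustained windows. That is window 1 × window 3, or window 2 × window 3 if the initial transient is excluded. The second choice separates less sharply, because those windows are only 1300 − 1000 = 300 ms apart at the nearest edge. A code of width 200 ms still gives exp(−300²/(2·200²)) ≈ 0.32 of its peak there.
- **GNW, PFC:** group-level decoding above chance in the onset × offset cells, with no generalization to the windows in between. The Bayesian analysis already planned in Statistical approach suits the absence part better than a non-significant result.

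State the model matrices and how the diagonal is treated. If a regression is used as well, include diagonal, onset-block and offset-block nuisance matrices beside the two theory matrices, and do not rely on it alone.

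The cost is analysis wording, some extra computation and a slightly stricter criterion for each theory. No new data are needed.

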#### 3. Inter-areal communication: Patterns of synchronization

This analysis will focus on information sharing/integration between different cortical regions for each specific stimulus category.

GNW predicts that conscious perception, regardless of task, relies on long-range information sharing between nodes of PFC and Fusiform Face Area (FFA) when seeing a face, and PFC and Lateral Occipital Cortex (LOC) when seeing an object. This implies that synchronization within these regions should be more consistent across tasks (for a given stimulus category) than across stimuli (for a given task). IIT predicts strong bindings (‘relations’) between category-selective areas and lower-level visual areas, which again should be found regardless of the task. Hence, patterns of synchronization should be found between category-selective regions (FFA and LOC) and early visual cortex: specifically, between FFA and V1/V2 when seen faces (but not other stimulus categories) and between LOC and V1/V2 when seen objects (but not other stimulus categories). This synchronization should be more consistent across tasks than across stimuli.

#### 4. Putative NCC analysis

We will also perform further analyses to delineate the putative NCC for which GNW and IIT provide different predictions (PFC vs. posterior hot zone, respectively), after ruling out areas based on task contrasts (see the OSF preregistration for more details). To that end, we will run three contrast/conjunction analyses, which can be performed on univariate fMRI activation maps as well as on multivariate fMRI decoding maps: (A) Areas that are sensitive to *task goal (attending*, *detecting*, *& responding to target stimuli)*, showing greater activity for task-relevant targets vs. baseline (blank inter-trial intervals), and–importantly–no differential activity for non-targets (both for task-relevant or task-irrelevant) vs. baseline (blank ITIs); (B) Areas that are sensitive to *task-relevance (attending & detecting stimuli of the relevant categories)*, and accordingly are responsive to all task-relevant stimuli, whether targets or not, but are not responsive to task-irrelevant stimuli; (C) *candidate areas for enabling conscious perception (putative NCCs)*. We will look for the conjunction of areas sensitive to changes in the content of consciousness (stimulus present vs. blank ITIs) within each stimulus category (e.g., faces vs. blank, objects vs. blank, letters vs. blank, false fonts vs. blank).

The first two analyses (A & B) are aimed at *identifying areas that are most likely involved in the consequences of consciousness and are unlikely to be related to neural processes mediating consciousness per se*. The third analysis (C) is aimed at identifying *areas that may contain NCCs and/or sensory precursors to visual consciousness*. We note that the proposed contrasts might underestimate the consequences of consciousness (analysis A and B) and overestimate the NCC (analysis C). We have adopted a conservative approach which has the advantage of firmly, while not exhaustively, distinguishing between areas that might participate in consciousness vs. those that definitely do not. GNW predicts that the putative NCC should include prefrontal cortex after ruling out areas based on task contrasts. IIT in turn predicts that the putative NCC should be mapped primarily onto posterior areas, after ruling out areas based on task contrasts.

*Pilot data*. To establish the adequacy of our experimental protocols, this experiment has been pilot-tested for behavioral and eye movement patterns. The results of these pilot studies are reported on the OSF page (https://osf.io/6vgy3/). We also conducted a control experiment testing the visibility of the stimuli in an offline, surprise memory test. These pilot tests showed that subjects detect the targets with high sensitivity and specificity while being able to maintain fixation on the stimulus throughout the duration of the trial. They further confirmed that subjects were indeed aware of all stimuli, including the task-irrelevant ones, as performance and confidence for task-irrelevant stimuli was overall similar to task-relevant stimuli.

### Experiment 2

#### Aim

The general goal of Experiment 2 is to measure brain activity elicited by salient visual stimuli that are reported as seen versus unseen in the context of a secondary task. Stimulus visibility is manipulated via attention, by using an engaging video game as a primary, attentionally-taxing task. As such, this experiment predominantly evaluates the neural mechanisms underlying conscious vs. unconscious processing. Several predictions of GNW and IIT will be tested. GNW’s hypotheses are directly related to the contrast between reported-seen and reported-unseen trials, while IIT’s predictions focus on seen trials across different task manipulations. The most critical tests of GNW relate to the decodability of conscious content in prefrontal areas for seen stimuli, regardless of task manipulations, as well as the prediction that ignition of the global workspace (information sharing)–as measured by long-range synchrony between the prefrontal and sensory cortices–is key to conscious perception (again, regardless of the task). IIT’s central prediction in this experiment is that activity and patterns of connectivity within posterior cortical areas will be consistent across all task conditions for seen stimuli triggering similar experiences (within the same category), but different for seen stimuli triggering different experiences (across different categories), independently of the task in which those seen stimuli are embedded.

#### Design, stimuli, and procedure

We seek to measure brain activity elicited by salient stimuli reported as seen versus unseen due to inattentional blindness [55], in an attentional-taxing, engaging video game context. To minimize the relevance of the critical stimuli, subjects will be challenged to maximize performance on the video game, with visibility reports serving as a de-emphasized secondary task. This experiment will focus on investigating differences in activation, decoding, and level of inter-regional synchronization between seen and unseen stimuli, including prestimulus responses as well as early vs. late post-stimulus responses.

Large (2.3°), high contrast, faces and objects will be presented for 250 ms at one of four locations (two in the left, two in the right visual field, 6.4° eccentricity), while scrambled texture patterns [56] made from superimposing faces and objects will be presented at the other three locations. The stimuli will be displayed on top of rotating square shapes in the background of a video game, which spans the entire screen (to estimate the relative size of the stimuli compared with the background, see Fig 3).

**Fig 3 pone.0268577.g003:**
[figure not shown]
Experiment 2 design–A) The four worlds of the game, with four levels in each world (left). In worlds 1 & 3 (middle) the player will control a shiny blue orb at the bottom of the screen to collect falling disks of the same color (on three vertical tracks), while avoiding falling disks of a different color. The size of the full game display in visual angle is indicated here (panel A, middle). In worlds 2 & 4 the colors will be swapped and players will control an orange orb (right). B) Examples of stimuli presented in the background (central portion of screen blown-up for display purposes): face (left), object (middle), blank (right). C) During gameplay, at 3-6sec intervals (4-7sec for fMRI), an object/face/blank will appear on one of four background squares (middle) for 500ms total, 250ms at full contrast, followed by 250ms of fade-out. On some trials (every 9-18sec), the stimulus will be immediately followed by an awareness probe (right) in which the game will pause and a small arrow will appear in the center instructing subjects to report whether they had just noticed a stimulus in that location. D) Schematic of the background animation demonstrating the trial timing, stimulus timing, and probe timing. For a video demonstration of the video game, visit the preregistration website: https://osf.io/b9nce/).

In the *attended* (AT) condition, the same visual display as in the dAT condition will be presented, serving as a ‘replay’ of the video game, but with the opposite instruction: ignore the video game, and “be on the lookout” for either faces or objects appearing in the background. Eight different runs of the AT condition will be performed: during four of these runs, subjects will be instructed to press a button when they see a face, but not when they see an object, such that faces elicit a “go” response and objects a “no-go” response (and vice versa). We assume that in the AT condition stimuli will be easily seen, as they are presented for a long duration, and subjects’ only task will be to detect these stimuli (rather than playing the game as in the dAT condition). The crossing of the go/no-go task in the AT condition will yield two different trial types: AT-go-seen, and AT-nogo-seen, defined for both categories of stimuli (faces and objects). Both dAT and AT tasks will consist of several short runs, to allow for training and testing of classifiers on independent runs. The AT condition will thus serve both to define the ROIs for the dAT condition, and as an independent condition, to enable tests of generalization of decoding across the AT and dAT conditions.

Formally, Experiment 2 uses a nested factorial design with three factors: stimulus category (faces, objects), stimulus location (left, right), and task (distracted attention, attended). An additional factor will be measured but not manipulated: visibility (seen, unseen), which will be based on subjects’ reports in the distracted attention condition. We are particularly interested in the interactions between stimulus category (and location) and visibility, as well as stimulus category (and location) and task. A summary of trial types is presented in Table 1. Trial numbers, stimulus randomization and timing parameters will be optimized for the different methodologies i.e., fMRI, M-EEG and iEEG. Technique specific details are described in the preregistration in OSF.

**Table 1 pone.0268577.t001:** Trial types.

Trial type	Label	Trial description
DISTRACTED-ATTENTION Reported-Seen	dAT-seen	Faces/objects reported as “seen” in the awareness probes
DISTRACTED-ATTENTION Reported-Unseen	dAT-unseen	Faces/objects reported as “unseen” in the awareness probes
DISTRACTED-ATTENTION Blanks	dAT-blank	Background changes identical to face/object trials, but with no face or object presented, and correctly reported as “no” in the awareness probes
ATTENDED Seen-Go	AT-seen-go	Faces/objects in the AT task that are the target category eliciting a go response
ATTENDED Seen-Nogo	AT-seen-nogo	Faces/objects in the AT task that are not the target category and thus elicit a no-go response
ATTENDED Blanks	AT-blank	Background changes identical to face/object trials, but with no face or object presented in the AT task

#### Participants, sample size, exclusion criteria and stopping rule

Whenever possible, we aim at using the same subjects and sample sizes in both experiments. As in Experiment 1, the data will be monitored for quality during the data collection phase of the project, and we will stop collecting data upon completing the pre-defined sample size.

We will use comparable exclusion criteria as in Experiment 1. Here subjects will be included if performance in the AT task is: >80% hits, <20% FAs for fMRI and M-EEG subjects; >65% hits, <40% FAs for iEEG patients or if there is at least a 25% increase in hit rates in the AT task vs. seen rates in the dAT task. In addition, subjects will be excluded if they have too few seen/unseen trials in the dAT condition to conduct proper analyses (for a given stimulus category, if seen or unseen trial counts are <30 for M-EEG or <20 for fMRI. If analyses show that a good enough signal can be obtained with fewer trials, these numbers will be amended).

